## Methods

### Study design, population, and randomization process

The SI! Program Reintervention for Elementary Schools is a cluster-randomized trial, with schools serving as the units of randomization. In Spain, elementary education spans 6 grades and typically includes children aged 6 to 11 years. Eligible schools included public schools and charter schools initially limited to the Central, South, and East administrative areas defined by the Department of Education of the regional government of Madrid (Community of Madrid), as well as the city of Mataró (Barcelona province, Catalonia). To be eligible, schools also had to include at least one first grade class and have an operational canteen.

All schools meeting the inclusion criteria in the study areas were invited to attend informational meetings. Participation was voluntary at the school level and largely determined by institutional decisions and logistical constraints. Of the 1,026 schools in Madrid and 32 in Mataró that were invited, 50 agreed to participate. One additional school from the West administrative area of Madrid, geographically close to the boundary with the Central area, volunteered to participate and was included because it met all prespecified inclusion criteria. One school subsequently withdrew, resulting in 50 schools included in the study. Participating schools were part of the regular school systems in the study areas and represented diverse socioeconomic contexts, including public and publicly funded private schools. To reach the required sample size (see Sample Size Calculation), recruitment was conducted over 2 consecutive academic years, resulting in 2 enrollment phases: phase I (2023-2024) and phase II (2024-2025). In all, 36 schools from phase I and 15 from phase II agreed to participate (44 from Madrid and 7 from Mataró). Using block randomization stratified by school type (public vs charter), schools were assigned in a 1:1 ratio to either the reintervention group or the single-intervention group. Schools in the reintervention group were allocated to receive the SI! Program from second to sixth grade, with classroom interventions in both second and fifth grades, whereas those in the single-intervention group were allocated to receive the intervention from fifth to sixth grade, with a single classroom intervention in fifth grade (Figure 1). Schools were randomized consecutively in blocks of 6 by an independent researcher, and group allocations were communicated by email.

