#### Statistical analysis plan

The descriptive analysis will summarize baseline data, including demographic variables (eg, gender, age, place of birth), socioeconomic indicators (eg, household income, parental or caregiver education level and country of birth), and study-specific variables (eg, SI!-Child scores; lifestyle habits such as diet, sleep, and PA; adiposity measures; and blood parameters). Continuous variables will be presented as means and SDs, and categorical variables as frequencies and percentages.

Primary endpoint differences will be evaluated using all available measurements at baseline and at 5-year follow-up. The intervention effect will be estimated using multilevel mixed-effects models for repeated measures. The model will include fixed effects for time of assessment (baseline vs follow-up), randomization group (reintervention vs single-intervention), and the interaction between time and randomization group. The treatment effect will be estimated from the time-by-randomization interaction term, representing the between-group difference in change in SI!-Child score over time. Random intercepts for school and participant will be included to account for clustering at the school level and repeated measurements within individuals. Similar multilevel mixed-effects logistic regression models will be applied for categorical outcomes, and the same analytical strategy will be used to evaluate secondary endpoints.

The primary analysis will follow the intention-to-treat principle, including all randomized enrolled participants according to their allocated group. Models will be estimated using maximum likelihood, which provides valid inference under a missing-at-random assumption and uses all available data without requiring imputation. Models may additionally adjust for prespecified baseline covariates (eg, baseline outcome value, age, gender, and stratification variable) to improve precision.

Sensitivity analyses will be conducted to evaluate the robustness of the findings to alternative assumptions about missing data. These will include 1) complete-case analyses restricted to participants with both baseline and follow-up outcome measurements; 2) multiple imputation procedures; 3) additional sensitivity analyses exploring potential missing-not-at-random mechanisms, and other statistical approaches such as cluster-level analyses or Analysis of Covariance models of follow-up outcomes adjusted for baseline values.

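### The baseline SI!-Child score is already a response in the repeated-measures model; offering it as an optional covariate too cannot improve precision and makes the standard error too small

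*Protocol article*

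**What the plan says.** All of this is in the Statistical analysis plan section of the protocol article, except the randomization.

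- Responses: "Primary endpoint differences will be evaluated using all available measurements at baseline and at 5-year follow-up".
- Fixed effects (last word of the sentence cut): "The model will include fixed effects for time of assessment (baseline vs follow-up), randomization group (reintervention vs single-intervention), and the interaction between time and randomization".
- Effect of interest: "The treatment effect will be estimated from the time-by-randomization interaction term, representing the between-group difference in change in SI!-Child score over time".
- Random effects: "Random intercepts for school and participant will be included to account for clustering at the school level and repeated measurements within individuals".
- Estimation: "Models will be estimated using maximum likelihood, which provides valid inference under a missing-at-random assumption".
- Optional adjustment, in the same paragraph as the estimation method: "Models may additionally adjust for prespecified baseline covariates (eg, baseline outcome value, age, gender, and stratification variable) to improve precision".
- A separate sensitivity analysis in the next paragraph: "Analysis of Covariance models of follow-up outcomes adjusted for baseline values".
- Randomization (Study design, population, and randomization process): "Using block randomization stratified by school type (public vs charter), schools were assigned in a 1:1 ratio".

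Because ANCOVA is listed on its own as a sensitivity analysis, the covariate sentence refers to the mixed models described just before it. No covariate-by-time term is mentioned.

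**The concern.** With the baseline score on both sides of the equation, half of the response vector is regressed on itself. The baseline rows then fit almost perfectly, and their tiny residuals are pooled with the follow-up residuals into one residual variance. The participant random intercept, which should carry the within-child correlation, has nothing left to explain. The standard error of the interaction is built from these variances, so it shrinks although the estimate is no more stable.

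The stated purpose, precision, also fails for the other covariates named. A time-constant main effect adds the same amount to a child's two scores and cancels from the child's change, and change is what the interaction compares.

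At stake is the confidence interval and p-value of any adjusted analysis that takes up the option. The same strategy is to be used for the secondary endpoints.

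**Working it through.** **Inputs from the article.** SD 11.77, mean 70.62, ICC 0.05, average of 20 children per school, coefficient of variation of school size 0.51 (Sample size calculation); 26 vs 24 schools and 588 vs 389 children (Figure 2 legend).

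**Assumptions.** r = 0.3, 0.5 or 0.7; loss to follow-up 0% or 20%, completely at random; a school effect that does not change over time; one prognostic covariate explaining 15% of outcome variance.

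**The plan's own figure.** 5% of 70.62 is 3.531 points, which needs 175 children per arm without clustering. The design effect is 1 + ((1 + 0.51²) × 20 − 1) × 0.05 = 2.210. Then 175 × 2.210 = 386.8 children, or 19.3 schools, rounded up to 20 per arm. The stated 40 schools reproduce, and this point does not affect them.

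**Algebra, complete pairs.** Scale the score to variance 1 within each arm and time point.

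1. The pooled slope on the baseline score is b = (1 + r)/2.
2. Residual variance at baseline: (1 − b)² = (1 − r)²/4.
3. Residual variance at follow-up: 1 − 2br + b² = (1 − r)(5 + 3r)/4.
4. Covariance of a child's two residuals: (1 − b)(r − b) = −(1 − r)²/4. It is negative, so the participant variance is estimated at zero.
5. Pooled residual variance, the mean of steps 2 and 3: (1 − r)(0.75 + 0.25r). The correct within-child variance is (1 − r).
6. The estimate is still the difference in mean change. So reported SE / true SE = √(0.75 + 0.25r), and type I error = 2[1 − Φ(1.96 √(0.75 + 0.25r))].

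For r = 0.3 / 0.5 / 0.7 the SE ratio is 0.908 / 0.935 / 0.962 and the type I error is 7.5% / 6.7% / 5.9%.

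**Algebra with a fraction m lost.** Now b = (1 + r(1 − m))/(2 − m), and the pooled residual variance is [(1 − b)² + (1 − m)(1 − 2br + b²)]/(2 − m). Children seen only at baseline add more near-zero residuals. At r = 0.5 and m = 0.2, b = 0.778 and the pooled variance is 0.395; times 11.77² this is 54.7, against 54.3 in the simulation below.

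**Simulation.** The article's linear model was fitted by maximum likelihood to 2,000 null trials per scenario, with critical value 1.96. The Monte Carlo standard error is about 0.5 percentage points at 5% and 0.7 at 10%.

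| r | Loss | True SD, without / with baseline covariate | Mean reported SE, without / with | Type I error, without / with |
|---|---|---|---|---|
| 0.3 | 0% | 0.883 / 0.883 | 0.913 / 0.827 | 4.1% / 6.9% |
| 0.5 | 0% | 0.780 / 0.780 | 0.772 / 0.721 | 5.7% / 6.8% |
| 0.7 | 0% | 0.583 / 0.583 | 0.598 / 0.574 | 4.7% / 5.8% |
| 0.3 | 20% | 0.982 / 0.992 | 0.985 / 0.838 | 5.2% / 9.9% |
| 0.5 | 20% | 0.843 / 0.850 | 0.840 / 0.726 | 5.4% / 10.3% |
| 0.7 | 20% | 0.683 / 0.688 | 0.658 / 0.577 | 5.1% / 10.1% |

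With complete pairs the estimate moved by less than 10⁻¹² in every trial. The mean SE ratio was 0.906 / 0.933 / 0.960, as the algebra predicts. The participant variance was 0.00 in all six scenarios with the baseline covariate. With 20% loss the SE ratio was 0.851 / 0.864 / 0.876, while the true spread of the estimate rose slightly.

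**Other covariates.** The prognostic main effect gave an SE ratio of 1.000 with complete pairs and 0.993 / 0.995 / 0.997 with 20% loss, and its type I error stayed near 5%.

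**ANCOVA of the follow-up score.** The reported SE agreed with the true SD to within about 4%, and type I error was 5.6% to 6.8% with normal critical values. With complete pairs its true SD (0.917 / 0.786 / 0.590) was no smaller than that of the unadjusted mixed model.

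**The case against.** The strongest reply is that the primary model is sound as specified. The article commits to time, group, their interaction and two random intercepts. The covariates come afterwards, in permissive wording and as examples. This stands: the plan can be followed in full without the faulty term, and the unadjusted model held its type I error at 4.1% to 5.7%. The correct use of baseline, ANCOVA, is also already listed.

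A reader might go further and infer any of the following, none of which the article supports.

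- *That the planned primary result is anti-conservative.* Only an analysis that takes up the baseline-outcome option is affected.
- *That covariate adjustment in general spoils the standard error.* Only the baseline outcome does; a main effect of the age, gender or school-type kind left the error rate alone.
- *That no main effect can ever sharpen the interaction.* This is exact for the linear model with complete pairs. With loss there was a gain, though under 1% in SE. The logistic models were not examined.
- *That permissive wording leaves a choice of p-values after unblinding, or that the stratification variable must be made compulsory.* The sentence calls the covariates prespecified, and the final list may properly sit in an analysis plan that is not shown.

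What the reply does not rescue is naming the baseline outcome as a covariate of a model in which it is a response, for a benefit that it cannot give.

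**Conclusion.** The point holds for one named option. Used in the repeated-measures model, the baseline outcome covariate leaves the interaction estimate unchanged with complete pairs and understates its SE by about 4% to 9% for r from 0.7 down to 0.3. Type I error is then about 5.9% to 7.5%. With 20% loss the SE is about 12% to 15% below that of the unadjusted model, and type I error is about 10% in simulation.

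Neither r nor the loss rate is in the article. The plan's increase from 40 to 42 schools is an allowance of 2/42, about 5%, so 20% is an illustration for a 5-year follow-up and not the plan's figure. The sizes also rest on loss completely at random, a time-constant school effect and the linear model.

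The other listed covariates do no harm, but the stated reason for including them does not apply to the interaction to any useful extent.

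**What to change.** In the Statistical analysis plan section:

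1. Delete the baseline value of the outcome from the covariates of the repeated-measures models.
2. State that baseline is used either only as a response (the mixed model as specified, or one with a common baseline mean) or only as a covariate (the ANCOVA of the 5-year score already listed as a sensitivity analysis).
3. Drop the claim that main-effect covariates improve the precision of the interaction. A covariate meant to sharpen it should enter with its time interaction or through the ANCOVA. A time interaction helps only as far as the covariate predicts change, and no such gain was calculated here.

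The cost is a change of wording. No new data are needed and the sample size is unaffected. By the study timeline, which runs to 2031, it can be made well before the 5-year scores exist.

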## Discussion

Over the past 50 years, widespread lifestyle changes and an increase in cardiovascular risk factors—such as obesity, hypertension, dyslipidemia, and diabetes mellitus—have contributed to a global rise in the incidence and prevalence of cardiovascular events, including heart failure and stroke.^13^^,^^38^ At the same time, preventive strategies promoting healthy lifestyles have helped reduce cardiovascular mortality rates.^13^^,^^38^ Despite these gains, determining when and how to intervene to preserve CVH from early childhood remains a persistent challenge.

The SHE Foundation, in collaboration with CNIC (*Centro Nacional de Investigaciones Cardiovasculares*, Spanish National Centre for Cardiovascular Research), has developed and evaluated multiple health promotion programs that use education as a tool for cultivating healthy habits from childhood through adulthood, to foster a culture in which people of all ages prioritize health and well-being.^7^^,^^39^ Similar programs targeting children and adolescents exist worldwide.^40^ While childhood is widely recognized as a critical period for establishing lifelong health behaviors,^41^ it is not sufficient to address a single cardiovascular risk factor—such as obesity—or to focus on a single population subgroup.^42^ Instead, a comprehensive approach is needed that integrates emotional, behavioral, and environmental dimensions across the broader community.^7^^,^^41^^,^^43^ The life-course approach provides a compelling framework for this purpose: supporting health and its social determinants across all life stages increases healthy life expectancy and generates significant individual, societal, and economic benefits.^43^

Primordial prevention strategies aim to halt the emergence of risk factors before they lead to clinical disease. In this context, urban provisioning systems—encompassing food, water, energy, transportation, buildings, and sanitation—have been extensively studied and are increasingly integrated into public health and sustainability planning.^44^ However, population-wide education, particularly at early stages of life, remains underemphasized in many of the frameworks and reports guiding these efforts.^43^^,^^44^

The Transtheoretical Model of Health Behavior Change outlines 6 stages of individual change: precontemplation, contemplation, preparation, action, maintenance, and termination.^45^ According to this model, improvements in health literacy can initiate progress through these stages—beginning with changes in knowledge (precontemplation and contemplation), followed by shifts in attitudes (preparation), and ultimately producing sustained behavior change (action, maintenance, and termination).^7^ In this light, education becomes a cornerstone of preventive health strategies, offering a low-cost, scalable alternative to more invasive interventions.

To fully realize the benefits of prevention, scientific knowledge must be translated into practical, community-level action—beginning at the household level and extending to the neighborhood. This includes fostering healthy diets, expanding opportunities for PA, supporting effective emotional regulation, and promoting smoking cessation. For this to succeed, science must be embedded in society, and society must, in turn, be empowered to act on science.

In the upcoming trial of the revised SI! Program (Central Illustration), the whole-school strategy underscores the importance of collective action in promoting meaningful and sustained health behavior change.^46^^,^^47^ By engaging multiple stakeholders—students, educators, school staff, and families—particularly through the *Leading group* and the *Healthmeter* tool, the program fosters a shared sense of ownership and responsibility for health-related goals.

**Central Illustration fig5:**
[figure not shown]
**Design of the School-Based SI! Program Reintervention Trial** This cluster-randomized controlled trial enrolled 977 children from 50 public and charter schools in Madrid and Barcelona, Spain. Schools were randomized to one of 2 arms: a reintervention group (first intervention in second grade and reintervention in fifth grade) or a single-intervention group (intervention only in fifth grade). This revised SI! Program builds on insights from earlier trials, emphasizing adherence and long-term behavior change through a reintervention strategy on socioemotional learning combined with active engagement of the school community and families. The goal is to strengthen the program's impact—assessed by the SI! Child lifestyle score—and support the adoption of lasting healthy habits, thereby contributing to the reduction of cardiovascular disease burden.

This collective approach not only distributes workload and accountability but also strengthens motivation and commitment across the school community. Within this model, collective action serves as a catalyst for reinforcing social norms around health, encouraging peer support, and embedding health-promoting practices into the rhythms of daily school life through resources such as posters, stickers, and structured daily routines.

Equally important is the program’s emphasis on participatory processes, which enable members of the school community to shape actions according to their needs, values, and local context. This approach aims to increase the relevance and acceptability of activities, while also helping to shift power dynamics by elevating the voices of students and less formally recognized contributors, such as support staff and parents/caregivers. This inclusive model of engagement has the potential to foster a platform for continuous feedback and adaptation. Together with the program’s reintervention strategy, this emphasis on inclusion may represent a key mechanism for achieving long-term impact.

The revised design aligns implementation timing with teachers’ capacity to deliver the curriculum effectively, supporting adherence at levels associated with the greatest impact—defined as completion of more than 75% of program content.^2^^,^^3^ Beyond the collective intervention strategy, the strengthened focus on SEL—specifically targeting emotional regulation—adds an innovative dimension that may further enhance effectiveness, given its strong links to the adoption and sustained practice of healthy behaviors.^48^^,^^49^ The active involvement of the entire school community in periodic reinterventions that incorporate SEL may be essential for embedding health promotion into school routines and maximizing long-term impact.

One of the key innovations in the revised SI! Program is the introduction of the SI!-Child score, adapted from the American Heart Association’s recently proposed LE-8^50^ which includes clinical metrics that require blood sampling. However, because clinical measures often remain unaltered over the short term, such composite scores may be less suitable for detecting the effects of primordial prevention strategies in young populations.^6^ The SI!-Child score was designed as a simple, reliable, and easy-to-use tool for assessing and tracking CVH in children and adolescents.

Other screening tools that focus on lifestyle and other risk factors while excluding laboratory measures have proved to be reliable instruments for the assessment of CVH in adults.^51^^,^^52^ The Fuster BEWAT score (BP, Exercise, [body] Weight, diet [Alimentation], and Tobacco use) has been found to perform similarly to the Life’s Simple 7 score in terms of its ability to predict subclinical atherosclerosis, left ventricular abnormalities, and target organ damage.^53^, ^54^, ^55^ Such screening tools do not require specialized instruments or direct measurements, can be easily self-reported, and are particularly valuable in low- and middle-income countries where simpler and more comprehensive assessment methods are needed.^56^

The selection of appropriate evaluation tools is critical in any intervention trial. The integration of gold standard social science methods with minimally invasive biophysiological data collection represents a promising frontier in health promotion research.^13^^,^^57^ However, tools must be carefully tailored to participants’ age, cognitive development, and attention span.^58^ In early childhood, moreover, direct health indicators often show little change over short- to mid-term follow-up, since conditions such as dyslipidemia and hypertension are relatively uncommon in this population.^59^^,^^60^

This was evident in the SI! Program for Secondary Schools trial, where significant improvements in BP and cholesterol were difficult to detect, and behaviors such as smoking were uncommon (92.3% [95% CI: 90.7-93.6] of 12-year-olds reported never having smoked).^6^ Assessment tools must therefore be closely aligned with the research question and capable of detecting meaningful, age-appropriate changes, even if this means excluding other potentially valuable measures. For example, SI! Program trials with preschoolers^7^ used relatively simple KAH (Knowledge, Attitudes, and Habits) questionnaires, which may lack sensitivity when applied across broad age ranges that span considerable variation in cognitive development. Consequently, the trials in preadolescents^2^ and adolescents^6^ employed more complex instruments, such as those assessing PA^31^ and dietary intake via food frequency questionnaires.^26^^,^^61^

A good example comes from the SI! Program for Elementary Schools trial (1,770 children aged 6-11), which tested different intervention intensities across grades: content was either distributed evenly across the 6 grades (6-11 years), concentrated in the first 3 grades (6-8 years), or concentrated in the final 3 grades (9-11 years), with increased instructional hours allocated to the later years of Elementary School.^5^ While all the intervened groups showed significant improvements in several adiposity indicators, no changes were detected in KAH score. The *Lancet Diabetes & Endocrinology Commission* recently recommended confirming BMI estimates of excess adiposity through direct body fat measurement or additional anthropometric criteria—such as WC, waist-to-hip ratio, or waist-to-height ratio—using validated age- and gender-appropriate methods and cutoffs.^62^ In line with this recommendation, interventions should incorporate a broader set of indicators that more precisely reflect adiposity distribution and may capture differences not seen with traditional obesity measures, especially in this age range.^63^, ^64^, ^65^

Previous SI! Program trials found no between-group differences in BMI,^1^^,^^3^^,^^4^ but did detect favorable intervention effects on subscapular skinfold thickness in preschoolers^4^ and on WC and waist-to-height ratio in elementary school children.^5^ In the Elementary Schools trial, children in the intervention groups who began the program at age 6 showed significant improvements in adiposity markers after 6 years.^5^ Nevertheless, BMI was retained in the SI!-Child score, in line with American Heart Association recommendations for the LE-8.

Finally, the use of a CVH score derived from the LE-8 framework enables robust comparability across studies, thereby broadening the scope and applicability of the trial’s findings. At the same time, the exclusion of blood-based metrics enhances the SI!-Child score’s sensitivity to short- and mid-term changes in lifestyle-related behaviors—aligning with the SI! Program’s goal of promoting behavior change through periodic reintervention. Clinical indicators often remain within the ideal range throughout childhood and adolescence, potentially masking early declines in lifestyle-related CVH.^6^^,^^66^, ^67^, ^68^ Screening tools like the SI!-Child score are therefore essential for monitoring overall CVH and evaluating the effectiveness of health promotion programs in young populations.

